## Abstract

**Introduction:**

Pain constitutes a major component of the global burden of diseases. Recent studies suggest a strong genetic contribution to pain susceptibility and severity. Whereas most of the available evidence relies on candidate gene association or linkage studies, research on the genetic basis of pain sensitivity using genome-wide association studies (GWAS) is still in its infancy. This protocol describes a proposed GWAS on genetic contributions to baseline pain sensitivity and nociceptive sensitisation in a sample of unrelated healthy individuals of mixed Latin American ancestry.

**Methods and analysis:**

A GWAS on genetic contributions to pain sensitivity in the naïve state and following nociceptive sensitisation will be conducted in unrelated healthy individuals of mixed ancestry. Mechanical and thermal pain sensitivity will be evaluated with a battery of quantitative sensory tests evaluating pain thresholds. In addition, variation in mechanical and thermal sensitisation following topical application of mustard oil to the skin will be evaluated.

**Ethics and dissemination:**

This study received ethical approval from the University College London research ethics committee (3352/001) and from the bioethics committee of the Odontology Faculty at the University of Antioquia (CONCEPTO 01–2013). Findings will be disseminated to commissioners, clinicians and service users via papers and presentations at international conferences.

Strengths and limitations of this studyWe propose a genome-wide association study of both baseline pain sensitivity as well as nociceptive sensitisation.The study will be conducted in an admixed population in Colombia, with variable proportions of European, Native American and sub-Saharan African ancestry.Phenotypic data will be collected by a single trained examiner, thus producing high-quality measures.Because we are focusing on highly reproducible pain phenotypes obtained at a single centre, our initial sample size is limited to 1500–2000 participants. This will allow us to identify only genetic variants that have intermediate and large (but not small) effect sizes.

## Introduction

Pain constitutes a major component of the global burden of diseases, with lower back and neck pain representing the single leading cause for years lived with disability followed closely by migraine and other musculoskeletal disorders.^1^ Pain is a multidimensional experience involving a highly complex interaction of physical, biochemical, physiological, cognitive, emotional, behavioural and sociocultural factors. Many studies have identified genetic factors in a range of chronic pain conditions.^2^ Importantly, a growing number of studies in patient populations suggest that genetics is an important contributory factor to pain susceptibility and severity.^2–4^ Of note, twin studies using either clinical pain outcomes or experimental pain models suggest that sensitivity to pain has a heritability of up to 55%.^5–10^ Interestingly, the heritability varies greatly depending on the clinical pain outcome or the sensory modality tested in experimental pain models.^7^ There is evidence that different sensory modalities may have distinct genetic components contributing to their variance in humans,^10^ and this is consistent with animal models which underline the distinct neurobiology mediating different sensory modalities.^11^

A powerful technology for identifying genetic determinants of human complex phenotypes is genome-wide association studies (GWAS). However, GWAS analyses of pain remain limited, mainly due to the high numbers of individuals required to enable adequate power, and the complexities of accurately phenotyping traits that ultimately represent a personal subjective perception.^2^ In contrast to disease cohorts where pain variation may be influenced by the severity of the disease process or its treatment, experimental pain studies measuring baseline pain sensitivity have the advantage of studying one stimulus in a standard condition (eg, controlling intensity, location and stimulus duration). To date, several candidate gene studies have been performed to determine genetic influences on human pain sensitivity using experimental pain models,^5–9 12 13^ however, to our knowledge, a full GWAS has not yet been reported. One genome-wide study evaluated association for single nucleotide polymorphisms (SNPs) revealed by exome sequencing in a subset of twins cohort that were identified as having particularly high or low heat pain sensitivity. Using pathway analysis, there was significant enrichment for variants in genes of the angiotensin pathway.^14^ Whereas a direct link between experimental pain sensitivity and clinical pain severity is often not present,^15^ there is some evidence that findings from experimental pain models can be predictive of clinically relevant pathological pain such as postoperative pain.^16^ Irrespective of the association between experimental and pathological pain, understanding the genetic influences on experimental pain sensitivity will provide important biological insights into the mechanisms underlying pain sensitivity.

An important drawback of most genetic studies in the pain field so far is that they have been performed mostly in populations of European ancestry, thus, they have explored only a small fraction of human phenotypic and genetic diversity.^17 18^ This is important in the study of pain as recent studies point to variable pain thresholds for European Americans, African Americans and Latinos.^19–21^ However, it is not clear if this variation in pain thresholds relates to differences in neurobiological mechanisms or other factors such as social or cultural^22^ parameters. In addition, recent studies suggest that a phenotype associated with increased sensitisation of the nociceptive system due to temporal summation may render people vulnerable to developing clinically relevant pain.^23^ However, most studies focus on pain phenotyping in the naïve state rather than sensitised state; only a handful of studies have investigated a genetic component underlying nociceptive sensitisation.^7 24^ We, therefore, intend to use an algogen (allyl isothiocyanate [AITC], an agonist of the ligand gated ion channel TRPA1) in order to sensitise the nociceptive system to replicate the changes that could occur in pathological pain states.

This protocol proposes a GWAS on genetic contributions to baseline pain sensitivity and nociceptive sensitisation in a sample of unrelated healthy individuals of mixed European/Native American/African ancestry. We will evaluate baseline cutaneous pain thresholds as well as the variation in sensitisation following mustard oil (AITC) application, a controlled model of tissue injury. We hypothesise that we will identify SNPs associated with experimental pain stimuli in the naïve and sensitised state. Elucidating the genetic basis of pain variation has the potential to reveal targets for future analgesic development. This can be translated into improved pain management potentially tailored to an individual’s pain risk or resilience, including sensitivity differences between different human populations.

## Methods and analysis

This GWAS follows the Strengthening the Reporting of Genetic Association Studies guidelines.^25^ A flow chart of the study procedure is detailed in figure 1.

**Figure 1 F1:**
[figure not shown]
Study procedure. The graph details the study procedure from recruitment to data analysis. Yellow boxes represent new procedures; green boxes indicate data generation and collection; blue boxes indicate a procedural step. AITC, allyl isothiocyanate; BMI, body mass index; CANDELA, Consortium for the Analysis of the Diversity and Evolution of Latin America; CDT, cold detection thresholds; GWAS, genome-wide association study; HPT, heat pain threshold; MPT, mechanical pain threshold; PCs, principal components; PPT, pressure pain threshold; QST, quantitative sensory testing; TSL, thermal sensory limen; VDT, vibration detection threshold; VAS, Visual Analogue Scale; WDT, warm detection thresholds; WUR, wind-up ratio.

### Participants

Healthy participants aged 18–40 will be recruited in Medellin, Colombia via public noticeboards at local Universities, distribution of flyers and through the local print media. In addition, we are inviting previous participants from the Consortium for the Analysis of the Diversity and Evolution of Latin America (CANDELA)^26^ GWAS to participate in this project.

Recruiting healthy young participants has advantages in GWAS studies. They are less likely to have undetected illnesses or other problems that may influence their biological pathway of pain sensitivity. Young people will also have less overall accumulated exposure or risks from environmental (external) factors which may affect their pain sensitivity. Such factors increase the overall variability of participants’ pain perception response and reduce the power of detecting genetic causes. Since most traits are affected by a combination of genetic and environmental factors, many studies including CANDELA tend to use young participants for genetic variant discovery.^27^

Participants will be excluded if they have chronic pain or any chronic medical condition (eg, diabetes, neurodegenerative, musculoskeletal or psychiatric conditions). Participants currently taking analgesics, anti-inflammatories, opioids, antihistamines, antidepressants or antiepileptic drugs will be excluded. Women who are pregnant or in their menstrual phase (self-report) will be excluded from the study. Participants will be advised to not smoke or consume coffee within 1 hour of testing, and to avoid psychoactive substances or alcohol within 8 hours prior to testing. Further exclusion criteria include current or past self-inflicted injuries, as well as dermatomal, traumatic or infectious conditions affecting the arm, and a history of severe allergic reactions to any kind of medication, materials, food or insect bites. Participants with moderate to severe anxiety (≥25 on the Hamilton Anxiety Rating Scale^28^) or severe depression (>15 on the 16-item Quick Inventory of Depressive Symptomatology Self-Reported (QIDS-SR16)^29^ will be excluded from the study. Recruitment started in January 2013 and is predicted to take approximately 5–7 years.

### Procedure

Participants will attend a single appointment at the quantitative sensory testing (QST) laboratory at the Universidad de Antioquia, Medellín. Following informed consent, age and self-reported gender will be recorded and participants will answer questions regarding their self-reported ancestry (see online supplementary appendix 1). Height and weight will be measured and body mass index (BMI) calculated. Since psychological factors such as anxiety can influence pain perception during experimental pain testing,^30^ participants will complete the Spanish version of the Hamilton Anxiety Rating Scale and the QIDS-SR16. The QIDS-SR16 has acceptable internal consistency and moderate to strong concurrent validity compared with other depression scores^31^ and its Spanish version shows adequate test–retest reliability and high internal consistency.^32^ The Hamilton Anxiety Rating Scale has shown to have high inter-rater and test–retest reliability^33^ and good construct validity.^34^

10.1136/bmjopen-2018-025530.supp1Supplementary data

### Evaluation of sensory function in the naïve state

We will determine sensory function in the naïve state and following nociceptive sensitisation. Baseline sensory function will be evaluated using specific static and dynamic QST. These include cold detection threshold and warm detection thresholds, thermal sensory limen and heat pain thresholds (HPT) using a ThermoTester (Q-sense, Medoc, Israel, 30×30 mm thermode size). Recording of thermal thresholds will strictly follow published QST guidelines.^35^ Mechanical pain thresholds (MPT) will be evaluated using a 20 piece von Frey hair set (Touch Test, North Coast, USA) which exerts differing forces (9.8, 13.7, 19.6, 39.2, 58.8, 78.5, 98.1, 147.1, 255.0, 588.4, 980.7, 1765.2, 2942.0 mN). The von Frey hairs will be applied at a rate of 2 s on, 2 s off in ascending order starting from 9.8mN baseline stimulus until participants first perceive the stimulus as sharp (pricking). Subsequently, the hairs will be applied in descending order until the stimulus is perceived as blunt. The geometric mean of five series of ascending and descending stimuli is defined as the MPT. Wind-up ratio will be determined with numerical pain ratings on a Visual Analogue Scale (VAS 0–100) for a single stimulus followed by the average pain rating for a train of 10 stimuli applied at 1 Hz within the same 1 cm^2^ using a 255 mN von Frey hair. This will be repeated five times and the ratio will be established as the mean rating of the trains of stimuli divided by the mean rating of the single stimuli. Vibration detection thresholds (VDT) will be determined by recording the mean of 3 disappearance thresholds with a Rydel-Seiffer tuning fork. Pressure pain thresholds (PPT) will be recorded in triplicate with a manual algometer (Wagner Instruments, Greenwich, Connecticut, USA) and their mean used for analysis.

The side to be tested will be randomised and patients will first be familiarised with the sensory tests on the forearm on the control side, before performing the actual measurements on the test arm. All tests will be performed halfway over the volar side of the forearm except for VDT (ulnar styloid) and PPT (thenar muscles).

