#### Handling of missing data

It might not be possible to record some traits in some individuals, even though the completeness of the first 100 samples suggests that missingness will be low. The single-trait methods used in traditional GWAS analyses automatically exclude individuals from the analysis of a trait who have missing values for that trait. The same applies to individuals having missing genotypes for any particular SNP. However, genotyping success rate using the Illumina HumanOmniExpress chip in the CANDELA cohort is very high (>99.8%), so the number of excluded individuals in any analysis would be very low overall.

Some multivariate analyses such as PCs when applied on the set of phenotypes require having recorded values of all phenotypes for an individual. Instead of using the subset of individuals who have the complete set of phenotypes recorded, which would incur some loss in sample size, the missing phenotype data for each individual will be imputed following standard statistical procedures as implemented in the R package ‘mice’.^62^ When the proportion of missing data is small, imputation is preferable in such multivariate analyses than sample exclusion, and is routinely applied to genetic data such as while calculating genetic PCs.^58^

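### The wind-up ratio has no value when all five single-stimulus ratings are 0 and is unstable when their mean is near 0, yet it goes into a linear-regression GWAS

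*Protocol article*

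**What the plan says.** Protocol article, section *Evaluation of sensory function in the naïve state*: participants give "numerical pain ratings on a Visual Analogue Scale (VAS 0–100) for a single stimulus" and then an average rating for a train of ten, applied "within the same 1 cm^2^ using a 255 mN von Frey hair". After five repeats, "the ratio will be established as the mean rating of the trains of stimuli divided by the mean rating of the single stimuli". The same section lists the filament forces for the mechanical pain threshold (MPT); the upper end reads "147.1, 255.0, 588.4, 980.7, 1765.2, 2942.0 mN".

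The wind-up ratio (WUR) appears among the measures in the Figure 1 legend and in Table 1. Under *Data analysis plan*, each trait is taken singly into an additive linear regression across the genome.

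Section *Handling of missing data*: single-trait methods "automatically exclude individuals from the analysis of a trait who have missing values for that trait". For multivariate analyses such as phenotype principal components, "the missing phenotype data for each individual will be imputed following standard statistical procedures", using the R package mice. The section expects missingness to be low, judging from the first 100 samples.

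**The concern.** The scale includes 0, and everyone receives the same force. The MPT series continues above that force, so the design itself provides for people who do not find 255 mN sharp. A mean single rating of 0, or close to 0, is therefore foreseeable.

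Two problems follow.

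- **At exactly 0**, the trait has no value although both ratings were recorded. The natural coding is missing, and the missing-data rules would then apply. Exclusion would select the WUR sample on pinprick rating. Imputation under the usual missing-at-random assumption would fill in a value that is absent because of that rating. Some of these people may wind up strongly: no pain from one stimulus, clear pain from the train.
- **Near 0**, the ratio exists but is driven by a tiny denominator. A few extreme values then carry much of the variance in a linear regression. At a rare allele a handful of carriers can include one of them, so p-values far below nominal can arise by chance. The ratio is also tied inversely to the single rating, so a locus for single-pinprick sensitivity could look like a wind-up locus or hide one.

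**Working it through.** **Inputs from the protocol article.** Scale 0–100; force 255 mN; five repeats; ratio of means; 13 listed forces, of which 4 exceed 255 mN (588.4, 980.7, 1765.2 and 2942.0); thresholds 5×10⁻⁸ and 10⁻⁵. The planned sample reproduces: 0.50 × 2000 + 500 = 1500 and 0.75 × 2000 + 500 = 2000. The plan's power values are in Figure 3, which is not shown, so they could not be compared.

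**Step 1, when the ratio fails.** WUR = mean(T₁…T₅) / mean(S₁…S₅). The denominator is 0 only if all five S are 0. With a mean train rating of 10:

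| Single ratings | Mean single | Ratio | Train minus single |
|---|---|---|---|
| 0, 0, 0, 0, 5 | 1 | 10 | 9 |
| 0, 0, 0, 0, 1 | 0.2 | 50 | 9.8 |
| 0, 0, 0, 0, 0 | 0 | undefined | 10 |

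One rating moving from 5 to 1 multiplies the ratio by five. The difference moves by 0.8.

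**Step 2, how often (assumed inputs).** Let p be the share of single stimuli rated 0. With independent repeats, P(all five 0) = p⁵: 0.001% at p = 0.1, 0.24% at 0.3, 3.1% at 0.5. Repeats within a person are likely to be correlated. In a beta-binomial model with correlation ρ, put a = p(1/ρ − 1) and s = 1/ρ − 1; then P is the product of (a + k)/(s + k) for k = 0 to 4. For p = 0.1 and ρ = 0.5: (0.1 × 1.1 × 2.1 × 3.1 × 4.1)/(1 × 2 × 3 × 4 × 5) = 2.936/120 = 2.4%. For ρ from 0.5 to 0.8:

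| p | P(all five 0) |
|---|---|
| 0.05 | 1.1–3.2% |
| 0.1 | 2.4–6.5% |
| 0.2 | 5.9–13.7% |
| 0.3 | 10.6–21.6% |

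The answer depends almost wholly on p and ρ, and the documents give neither.

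**Step 3, power lost through smaller n.** Test: 1-df chi-square with non-centrality n·q²/(1 − q²), where q² is the share of trait variance explained. At 5×10⁻⁸ and n = 1500, 80% power needs q² = 2.57%, so the non-centrality is 1500 × 0.02572/0.97428 = 39.6. At n = 2000 the required q² is 1.94%. Losing a fraction f multiplies the non-centrality by 1 − f:

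| Assumed undefined | Power for that locus |
|---|---|
| 0% | 80% |
| 1% | 79.1% |
| 3% | 77.2% |
| 5% | 75.2% |
| 10% | 69.8% |

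The table is the same for n = 1500 and n = 2000, and covers lost sample only.

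**Step 4, the tail (illustrative simulation, assumed inputs).** With true wind-up independent of sensitivity and ratings bounded at 0 and 100, one setting with 1.5% undefined gave remaining ratios with skewness about 6, a maximum of 73 and a rank correlation of about −0.37 with sensitivity. Settings with 1%–8% undefined gave skewness of about 8–10. In these, type I error for the untransformed regression was about 40–60 times nominal at 10⁻⁴ for an allele frequency of 1%. A re-check with other assumed inputs gave the same direction with smaller skewness and inflation. Only the direction should be relied on.

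**The case against.** The strongest reply is that a zero-denominator rule and a trait transformation are details that a journal article may leave to the full protocol or analysis plan. That stands for a missing rule alone. Here, however, the article fixes the formula. Followed as written, it can yield no value, or an extreme one, for participants whose ratings were all recorded.

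Other points also carry weight:

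- The pilot speaks against a high undefined rate. Table 1 gives the WUR reliability as 0.634 (0.113 to 0.880) from 12 volunteers, an interval that fits about 11–12 usable pairs. At a 22% undefined rate, no loss among 12 has probability 0.78¹² = 5%. At 10% it is 0.90¹² = 28%, so a low rate is not excluded. An unstated zero rule could also explain complete pairs.
- The expectation of low missingness counts a little, but it is not specific to WUR and concerns traits that could not be recorded.
- Any allele-frequency filter in the supplementary quality-control appendix would limit the false-association problem.

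Three stronger readings are tempting, and the documents do not support them:

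- **One zero rating makes the ratio undefined.** It does not; all five must be 0.
- **The missing-data rule removes exactly the least pain-sensitive people.** The article never says that an undefined ratio counts as missing; that is an inference. Someone with a zero single mean and a non-zero train rating belongs at the high end of wind-up. Only 0/0 is uninformative.
- **The undefined share can be read from how many people have an MPT above 255 mN.** No MPT distribution is given. MPT is a sharp-or-blunt judgement, whereas WUR uses a pain rating. The longer filament series makes zeros foreseeable but does not measure how common they are.

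**Conclusion.** The point holds as a weakness of the stated trait definition. It should be corrected but does not threaten the study: only the WUR analyses and multivariate analyses that include WUR are affected, and everyone stays in the GWAS of every other trait recorded for them.

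That the ratio fails at a zero mean and is unstable near it follows from the formula and scale alone. How often this happens is unknown. The power loss is therefore a range under assumed rates: small at 1% undefined, about five points at 5% and ten points at 10%. The tail may matter more than lost sample, because it can distort the regression even when few ratios are undefined. Its size rests on assumed rating distributions and on the ratio being analysed untransformed, since the article states no transformation.

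**What to change.** - **Primary wind-up trait:** use a measure defined for every participant from ratings already recorded: mean train minus mean single, or mean train with mean single as a covariate.
- **Distribution:** check the residuals before the GWAS, or apply a rank-based transform.
- **Ratio:** keep it as a secondary measure and report how many values are undefined.
- **Imputation:** do not impute an undefined ratio. Enter the two mean ratings into mice and into the phenotype principal components.

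**Cost.** Analysis wording only; no new data. Results become less directly comparable with published ratios, which the secondary measure partly offsets. Adjusting for a single rating that may itself be heritable needs care in interpretation, because a locus can then appear through the covariate. The difference and the secondary ratio serve as checks on that.

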### Mustard oil evoked nociceptive sensitisation

After the baseline sensory measures, an acetate template will be used to mark a star with eight spokes each containing eight points at 1 cm increments on the volar forearm (figure 2). The skin temperature will be standardised by placing the 32°C warm thermode over the center of the star for 5 min before starting. We will then apply a sensitisation paradigm using mustard oil (AITC (Sigma), diluted at 30% in olive oil) as previously performed.^36^ AITC, the active component of mustard oil, activates the ion channel TRPA1 and evokes skin flare and nociceptive sensitisation.^37^ A small cotton swab soaked in mustard oil will be applied to a 0.64 cm^2^ area on the volar forearm and held in place with a Tegaderm (3M) for 10 min.^36^ During this time, pain scores will be recorded every 30 s using an electronic VAS ranging from 0 to 100. After 10 min, the mustard oil will be removed and the area of the skin flare will be recorded to the nearest 0.5 cm at each spoke.^7^ Eight triangular shapes will be created by joining the points on adjacent spokes and the total area will be calculated by adding all triangular segments. The area of mustard oil application will be subtracted from the total area to determine the area of secondary flare (flare area).

